#### Study Randomization

Patients undergo stratified randomization within centres based on the presence (or absence) of (i) a diagnosis of known or suspected COPD [31,32] or (ii) a central neurologic disorder, provided that a study ventilator is available. In the event that both diagnoses are present, we prioritize central neurologic disorders during stratification.

#### Weaning Procedures

Randomized patients are initiated on either the Automated Weaning or Protocolized Weaning algorithms until extubation criteria are achieved. All patients will be followed until successful extubation, ICU death, ICU discharge or until 90 days after randomization (deemed ventilator dependent).

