##### e) Reintubation and implications for ventilator management

In the Automated Weaning arm, a ventilator capable of delivering SmartCare™ is kept in the patient's room following extubation until the patient is deemed successfully extubated [off non-invasive (NIV) or invasive positive pressure ventilation for 48 consecutive hours]. Patients remain on the assigned strategy until ICU discharge, ICU death, successful extubation or until day 90 following randomization. Patients requiring reintubation in the Automated Weaning arm within 48 hours of extubation will be weaned using SmartCare™ as soon as possible (i.e., upon successful completion of a PST). All patients that require reintubation after successful extubation will be ventilated according to usual practice.

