#### Study Outcomes

The primary outcome of the WEAN pilot study is compliance with the weaning and sedation protocols. Secondary outcomes include (i) daytime clinician (nurse; RRT and physician) acceptance of the sedation and weaning protocols, respectively, (ii) time to successful extubation defined as the time from randomization to unsupported (no requirement for NIV or invasive ventilation), spontaneous breathing for ≥ 48 hours after extubation (or disconnection with a tracheostomy), (iii) time to completion of a successful SBT, (iv) total duration of mechanical ventilation (time from intubation to termination of ventilation), (vi) ICU and hospital length of stay, (vii) ICU and hospital mortality, and the proportion of patients (viii) developing nosocomial pneumonia [39], (ix) with weaning (self-extubation, tracheostomy, reintubation and prolonged mechanical ventilation >21 days) or ICU (myocardial infarction and pneumothoraces) complications, and (x) requiring NIV. Any NIV use is considered clinically relevant.

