#### Data Collection

We collect data at ICU admission, study inclusion and daily thereafter. Whereas protocol violations (non compliance) in the Automated Weaning arm include return to/remain on an alternate mode of mechanical ventilation in the absence of meeting criteria and any unauthorized interruptions (cessations, manual increases/decreases) in the automated protocol, violations in the Protocolized Weaning group include unauthorized use of modes other than pressure support (i.e., assist control) without criteria to return to or remain on an alternate mode of mechanical ventilation. We tabulate a daily score reflecting the number of SBTs conducted divided by the number of required SBT assessments in which all criteria were met in the Protocolized Weaning group. Sedation protocol compliance is assessed by the percentage of daily SAS scores < 2 or > 5 (or alternatively, RASS scores < - 4 or > +1) in both arms. We also evaluate compliance with the PEEP/FiO_2 _chart in both groups. RRT and physician acceptance of the weaning protocols and critical care nurse acceptance of the sedation protocol is assessed daily using Likert [40] scales [ranging from 0 highly unacceptable (extremely difficult to use) to 10 highly acceptable (extremely easy to use)].

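### Follow-up is stated to end at the same events as the weaning strategy, short of hospital outcomes and later ICU events that are listed as secondary outcomes

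*Protocol article*

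**What the plan says.** All places are in the Methods of the protocol article.

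- Weaning Procedures gives the end of follow-up: "All patients will be followed until successful extubation, ICU death, ICU discharge or until 90 days after randomization".
- Section e), on reintubation, gives the end of treatment by the same events: "Patients remain on the assigned strategy until ICU discharge, ICU death, successful extubation or until day 90 following randomization". It defines successful extubation as being "off non-invasive (NIV) or invasive positive pressure ventilation for 48 consecutive hours".
- The same section foresees events after that point: "All patients that require reintubation after successful extubation will be ventilated according to usual practice".
- Study Outcomes lists, among the secondary outcomes, "vi) ICU and hospital length of stay, (vii) ICU and hospital mortality". It also lists nosocomial pneumonia, weaning complications that include reintubation, and "ICU (myocardial infarction and pneumothoraces) complications, and (x) requiring NIV". Only prolonged ventilation carries a time limit (more than 21 days).
- Data Collection says: "We collect data at ICU admission, study inclusion and daily thereafter". It names no end.
- Statistical Analyses compares time to successful extubation and death between groups with a log-rank test.

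**The concern.** One set of events serves as both the end of treatment and the end of observation. Successful extubation normally comes before ICU discharge and always before hospital discharge, so the stated stop falls before several listed outcomes can be known. Two things are at stake.

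The first is loss of data. Hospital stay and hospital mortality need information from after the stop. So do ICU stay and ICU mortality in anyone extubated before leaving the ICU. In the time-to-death comparison, patients would leave the risk set because they had recovered, which is informative censoring.

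The second is unequal observation. The stop is also the efficacy event. If one arm is extubated sooner, it is watched for less time and can appear to have fewer complications at the same underlying risk. The pilot is meant to show whether a definitive trial is feasible, and that trial could inherit the rule.

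**Working it through.** **Which outcomes does the stated stop reach?** The article gives no figure to reproduce here, so the first step compares the stop with each listed outcome.

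| Outcome | Position relative to the stop |
|---|---|
| Compliance with weaning and sedation protocols (primary) | Inside |
| Self-extubation, reintubation or NIV within 48 h of extubation | Inside, because success requires 48 h off support |
| Ventilation beyond 21 days, tracheostomy | Largely inside |
| ICU stay, ICU mortality | Cut off in patients successfully extubated before ICU discharge |
| Later pneumonia, myocardial infarction, pneumothorax, NIV, reintubation | Cut off at extubation plus 48 h |
| Hospital stay, hospital mortality | Beyond the stop for anyone successfully extubated or discharged alive from the ICU |

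**How much ICU time lies after the stop?** The Background quotes medians from the five-centre European trial: total ventilation 9 versus 6.5 days, and ICU stay 15.5 versus 12.0 days (control versus SmartCare). As a rough difference of medians, 15.5 − 9 = 6.5 and 12.0 − 6.5 = 5.5 ICU days lie outside ventilation. If all of these follow extubation, taking off the 48-hour window leaves about 4.5 and 3.5 days after the stop.

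**How large could the unequal-time artefact be?** Inputs:

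- Median duration of ventilation of 4 versus 2 days from the same trial, used as a stand-in for time from randomization to extubation.
- The 48-hour window from section e).
- Assumptions not in the documents: exponential extubation times; a constant daily hazard h of 0.5% to 3%, equal in both arms and unchanged by extubation; no other reason for stopping; 1:1 allocation, so 45 per arm.

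With λ = ln 2 / median, λ = 0.1733 (control) and 0.3466 (automated). Mean observation is 1/λ + 2, that is 7.8 versus 4.9 days. The chance that an event is observed is

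P = 1 − exp(−2h) × λ / (λ + h).

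At h = 0.01:

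- Control: 1 − 0.9802 × 0.1733/0.1833 = 7.3%.
- Automated: 1 − 0.9802 × 0.3466/0.3566 = 4.7%.

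The last column below is the normal-approximation chance of p ≤ 0.05 in the direction of the artefact, Φ[(P₁ − P₂ − 1.96·SE₀)/SE₁], with SE₀ pooled and SE₁ unpooled. Without any difference it would be 2.5%.

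| Assumed h per day | Control | Automated | Chance of p ≤ 0.05 |
|---|---|---|---|
| 0.5% | 3.8% | 2.4% | 5.6% |
| 1% | 7.3% | 4.7% | 7.4% |
| 2% | 13.9% | 9.2% | 10.3% |
| 3% | 19.7% | 13.3% | 12.5% |

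The apparent relative reduction is about one third in each row (at 1%, 1 − 4.7/7.3 = 0.36), although the true risk is equal. If the arms share the same extubation times, both columns coincide and the artefact is zero.

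**Does a common window remove it?** Over one fixed window of w days, both arms have risk 1 − exp(−wh). With w = 28, chosen only as an illustration, and h = 1%, that is 24.4% in each arm.

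**The case against.** A reader might infer that the two statements cannot both hold, and that hospital outcomes will therefore not be obtained. The documents do not support that. The follow-up sentence sits under Weaning Procedures, directly after the one on how long the algorithms run, and its day-90 stop is tied to being deemed ventilator dependent, which is a weaning category. It may bound only the weaning course. Hospital stay and mortality can be read from the chart at discharge, and listing them as outcomes implies that someone will do so. This objection stands as far as intent goes. It does not rescue the wording: section e) already states the treatment period, whereas this sentence says that all patients are followed, and it is the only end of follow-up given. An article may leave the data-collection end date to the full protocol; here it states one that is too early for its own outcomes.

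A reader might also infer that the faster arm will show fewer complications. That is too strong:

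- The hazards are assumed.
- The medians come from the favourable earlier trial, while the Background also reports a single-centre Australian trial with no demonstrated reduction in weaning time.
- The Background links pneumonia and other complications to ventilation itself. If risk falls after extubation, fewer events are missed and part of any difference is real.

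Finally, the provision for late reintubation governs treatment, not data collection. It shows only that such events are foreseen.

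**Conclusion.** The point holds as a conflict between a stated follow-up rule and stated outcomes. It needs no assumption about event rates for hospital stay and hospital mortality, or for ICU outcomes in patients extubated before ICU discharge. The unequal-time bias is conditional. Under the assumptions shown it is an apparent reduction of about one third, for example 7.3% versus 4.7% at 1% per day, and it vanishes if extubation times are alike. With 45 per arm it would distort estimates more than tests, the chance of a significant result in that direction being about 6% to 13% instead of 2.5%.

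The scope is limited to secondary outcomes of a feasibility pilot. The primary compliance outcome is measured during weaning and is not affected. The text does not establish that the investigators intend to stop observing patients at extubation, only that the article says so. The correction should be made, but it does not call the main purpose of the pilot into question.

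**What to change.** - Reword the follow-up sentence in Weaning Procedures so that the four events end the assigned weaning strategy only, in line with section e).
- Add that mortality and length of stay are followed to hospital discharge, with a stated cap, for every randomized patient whatever the date of extubation. Run the time-to-death comparison on that follow-up.
- Count nosocomial pneumonia, myocardial infarction, pneumothorax, NIV and reintubation over one common window from randomization in both arms, and state its length. The investigators should choose it; the 28 days above are only an example.

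The cost is a few sentences and chart review to discharge for 90 patients, which the listed hospital outcomes already imply. If that review was always intended, only the wording and the choice of window remain. Vital status at a fixed day is not among the listed outcomes and is not needed for this correction.

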##### a) Ventilators

We use the Evita XL ventilator (which includes SmartCare™) or, alternatively, the Evita 2 dura or Evita 4 ventilators with a SmartCare™ ventilator upgrade in patients randomized to the Automated Weaning strategy. We equipped participating centres with a minimum of two of these ventilators. Comparable third generation ventilators (Evita 2 dura, Evita 4, Evita XL, Servo i, Servo 300, Puritan Bennett 840, Puritan Bennett 760, Avea or Galileo) are used in the Protocolized Weaning arm. We preferentially use Evita ventilators in the Protocolized Weaning arm if additional ventilators, when available.

##### b) Humidification systems and ventilator circuits

We clustered use of different forms of humidification to warm inspired air in the WEAN study to gain experience in the interaction of different forms of humidfication with the automated algorithm. We use heated humidifiers (MR850, Fisher & Paykel; Auckland, New Zealand) in both study arms in 5 centres and heat and moisture exchangers at 3 centres, to gain experience with the interaction between humidification and the Automated Weaning system. We record changes from one humidification strategy to another in the event difficulties (secretion volume, alarms etc) on the data collection forms. We use either RT 110 or RT 240 (Evaqua™) circuits in the WEAN study. Reusable circuits are not permitted.

##### c) Ventilator strategies and alarms

Regardless of the strategy to which the patient is randomized, the initial pressure support setting is similar to that used during the PST. In both groups, pressure support may increase or decrease during weaning according to patient needs or events (i.e., mucous plugging, anxiety). We present the details including initiation, titration and discontinuation) of the Automated Weaning and Protocolized Weaning strategies (in Additional file 1, Appendices 1 and 2). We set the maximum inspiratory pressure to 35 cm H_2_O in the Automated Weaning arm.

##### d) Criteria to suspend weaning protocols/return to an alternate mode of ventilation

In both groups, patients are permitted to return to or remain on alternate modes of ventilation for: (i) surgery or invasive procedures requiring sedation, (ii) respiratory distress defined by a) sustained hypoxemia (SpO_2 _< 90%) with FiO_2 _> 60% and PEEP > 10 cm H_2_O or hypercapnia with pH < 7.30 or clinical respiratory distress, b) repeated episodes (≥ 3 episodes within 1 hour wherein an inspiratory pressure (pressure support + PEEP) of 35 cmH_2_O is attained (despite suctioning, bronchodilation etc.), (iii) hemodynamic instability despite fluid boluses and the requirement for high dose vasopressors: norepinephrine > 15µg/min (0.2µg/kg/min) or equivalent, (iv) suspected myocardial ischemia based on electrocardiogram and/or elevated Troponin i, (v) neurologic deterioration with need to control PaCO_2 _(both groups) or alarm indicating "Central hypoventilation" (Automated Weaning), (vi) a requirement for increased sedation resulting in RR < 10 breaths/min. Patients meeting a criterion, are reassessed at least daily with PSTs to identify the earliest time when weaning can be resumed according to the assigned treatment. However, the pre-randomization requirement to undergo a SBT (if criteria are present) is not required at this time point.

##### e) Reintubation and implications for ventilator management

In the Automated Weaning arm, a ventilator capable of delivering SmartCare™ is kept in the patient's room following extubation until the patient is deemed successfully extubated [off non-invasive (NIV) or invasive positive pressure ventilation for 48 consecutive hours]. Patients remain on the assigned strategy until ICU discharge, ICU death, successful extubation or until day 90 following randomization. Patients requiring reintubation in the Automated Weaning arm within 48 hours of extubation will be weaned using SmartCare™ as soon as possible (i.e., upon successful completion of a PST). All patients that require reintubation after successful extubation will be ventilated according to usual practice.

##### f) Sedation titration

We developed a sedation guide to guide sedation administration and limit performance bias during weaning. Critical care nurses titrate sedation to achieve either a Sedation Agitation Scale (SAS) [33] score of 3 to 4 (see Additional file 1, Appendix 3) or a Richmond Agitation Scale Score (RASS) [34] of -3 to 0 [35]. Sedation titration is not mandatory in patients meeting criteria to return to or remain on an alternate mode of ventilation.

##### g) Other considerations

We developed a PEEP/FiO_2 _chart to guide their titration during weaning (see Additional file 1, Appendix 4). Use of the PEEP/FiO_2 _chart is not mandatory for patients meeting criteria to return to or remain on an alternate mode of ventilation.

Additional important considerations in developing the WEAN Study protocol include (i) the initiation and use of NIV following extubation [36,37], (ii) reintubation and reinitiation of weaning [38] and (iii) performance of a tracheostomy (Additional file 1, Appendix 5). For patients randomized to Automated Weaning, the data entered to initiate the system *mus*t be re-entered following a tracheostomy or change in humidification device prior to reconnection.

#### Study Outcomes

The primary outcome of the WEAN pilot study is compliance with the weaning and sedation protocols. Secondary outcomes include (i) daytime clinician (nurse; RRT and physician) acceptance of the sedation and weaning protocols, respectively, (ii) time to successful extubation defined as the time from randomization to unsupported (no requirement for NIV or invasive ventilation), spontaneous breathing for ≥ 48 hours after extubation (or disconnection with a tracheostomy), (iii) time to completion of a successful SBT, (iv) total duration of mechanical ventilation (time from intubation to termination of ventilation), (vi) ICU and hospital length of stay, (vii) ICU and hospital mortality, and the proportion of patients (viii) developing nosocomial pneumonia [39], (ix) with weaning (self-extubation, tracheostomy, reintubation and prolonged mechanical ventilation >21 days) or ICU (myocardial infarction and pneumothoraces) complications, and (x) requiring NIV. Any NIV use is considered clinically relevant.

#### Data Collection

We collect data at ICU admission, study inclusion and daily thereafter. Whereas protocol violations (non compliance) in the Automated Weaning arm include return to/remain on an alternate mode of mechanical ventilation in the absence of meeting criteria and any unauthorized interruptions (cessations, manual increases/decreases) in the automated protocol, violations in the Protocolized Weaning group include unauthorized use of modes other than pressure support (i.e., assist control) without criteria to return to or remain on an alternate mode of mechanical ventilation. We tabulate a daily score reflecting the number of SBTs conducted divided by the number of required SBT assessments in which all criteria were met in the Protocolized Weaning group. Sedation protocol compliance is assessed by the percentage of daily SAS scores < 2 or > 5 (or alternatively, RASS scores < - 4 or > +1) in both arms. We also evaluate compliance with the PEEP/FiO_2 _chart in both groups. RRT and physician acceptance of the weaning protocols and critical care nurse acceptance of the sedation protocol is assessed daily using Likert [40] scales [ranging from 0 highly unacceptable (extremely difficult to use) to 10 highly acceptable (extremely easy to use)].

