#### Statistical Analyses

Descriptive statistics including means, standard deviations, medians, interquartile ranges and frequency distributions will be used to summarize the data. For univariate analyses, we will use the Chi-square test (alternatively, Fisher's exact test when the expected value is ≤ 5) and Student's t-test (alternatively, the Mann-Whitney U-test, if normality assumptions are not satisfied) for binary and continuous outcomes, respectively. We will evaluate the percentage of (i) hours off-protocol and (ii) daily SAS scores < 2 or > 5 (or RASS equivalent) by treatment group. Compliance will be considered acceptable if ≥ 75% [that is; protocol violations (off protocol hours without meeting criteria to return to/remain on an alternate mode of mechanical ventilation) or SAS scores < 2 or > 5 (equivalent RASS -4 < or > +1) occur < 25% of the time]. SBT compliance will be considered acceptable if ≥ 75% of SBT opportunities are realized. We will compare average Likert scale scores based on clinician group and the weaning strategy utilized using Analysis of Variance (ANOVA). We will compare time to successful extubation and death between groups using time-to-event analysis with censoring of deaths and application of the log-rank test. We will consider p-values ≤ 0.05 to be statistically significant.

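### Sedation compliance, a named component of the primary outcome, is defined without the exemption that the protocol grants for sedation titration and applies to its weaning component

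*Protocol article*

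**What the plan says.** Study Outcomes in the Protocol article names two protocols: "The primary outcome of the WEAN pilot study is compliance with the weaning and sedation protocols". Four other places in Methods bear on the sedation part.

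- **f) Sedation titration** sets a target range and then limits the obligation: "Sedation titration is not mandatory in patients meeting criteria to return to or remain on an alternate mode of ventilation".
- **d) Criteria to suspend weaning protocols/return to an alternate mode of ventilation** lists six criteria. Two concern sedation directly: (i) "surgery or invasive procedures requiring sedation" and (vi) "a requirement for increased sedation resulting in RR < 10 breaths/min".
- **Data Collection** gives the measure: "Sedation protocol compliance is assessed by the percentage of daily SAS scores < 2 or > 5", or the RASS equivalent, in both arms.
- **Statistical Analyses** gives the bar, "Compliance will be considered acceptable if ≥ 75" per cent, which it explains as violations occurring less than 25% of the time. In that explanation a weaning violation means "off protocol hours without meeting criteria to return to/remain on an alternate mode of mechanical ventilation". The sedation term beside it carries no such condition.

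**The concern.** The pilot asks whether clinicians follow the sedation protocol. That question has meaning only for periods when the protocol asks something of them. The weaning term respects this, because time off protocol with a valid reason is not a violation. The SBT score in Data Collection does too, since its denominator holds only assessments at which all criteria were met. The sedation term alone is worded as a percentage of daily scores with no condition.

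A centre that acts within the titration exemption can therefore be scored non-compliant, for instance when a patient is at SAS 1 during a sedated procedure. In-range scores from the same exempt periods are credited as adherence to an obligation that did not apply. At stake is a feasibility verdict that informs whether a definitive trial goes ahead.

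**Working it through.** **The plan's own figure.** The 75% bar is the complement of the 25% violation limit: 1 − 0.25 = 0.75. It is a design choice with no derivation, so there is nothing further to reproduce.

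**What counts as out of range.** SAS below 2 or above 5 means SAS 1 or SAS 6–7. RASS below −4 or above +1 means RASS −5 or anything above +1. SAS 2 lies below the 3–4 target but is not counted.

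**Formula.** Let f be the share of scores taken while a suspension criterion is met, ve the out-of-range rate in those scores, and vn the out-of-range rate while titration is mandatory.

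- Violation rate over all scores: V = f × ve + (1 − f) × vn
- Violation rate that answers the compliance question: vn
- Shift: V − vn = f × (ve − vn)
- Exempt share at which V reaches 25%: f* = (0.25 − vn) / (ve − vn)

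The document gives none of f, ve or vn. All values below are assumptions, chosen to show a range.

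| f | ve | vn | V | Compliance, all scores | Compliance, mandatory scores | Verdict at 75% |
|---|---|---|---|---|---|---|
| 20% | 60% | 18% | 26.4% | 73.6% | 82% | pass becomes fail |
| 20% | 50% | 20% | 26.0% | 74.0% | 80% | pass becomes fail |
| 20% | 80% | 15% | 28.0% | 72.0% | 85% | pass becomes fail |
| 10% | 80% | 20% | 26.0% | 74.0% | 80% | pass becomes fail |
| 10% | 50% | 20% | 23.0% | 77.0% | 80% | unchanged |
| 5% | 80% | 20% | 23.0% | 77.0% | 80% | unchanged |
| 20% | 5% | 27% | 22.6% | 77.4% | 73% | fail becomes pass |

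First row in full: 0.20 × 0.60 + 0.80 × 0.18 = 0.120 + 0.144 = 0.264. The shift is 0.20 × (0.60 − 0.18) = 0.084, or 8.4 points.

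**Exempt share needed for a false fail.** With vn = 20% and ve = 80%, f* = 0.05 / 0.60 = 8.3%. With vn = 10% and ve = 50%, f* = 0.15 / 0.40 = 37.5%.

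**At 5% exempt.** With ve = 80%, V reaches 25% only when vn is at least (0.25 − 0.05 × 0.80) / 0.95 = 0.21 / 0.95 = 22.1%. The mandatory-period rate must already be close to the limit.

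**The case against.** The strongest reply is that this is a condensed article. It speaks of daily scores and never says that every score enters the denominator. Its phrase about sedation protocol compliance could be read as limited to periods when the protocol applied. The sedation guide is in an additional file that is not shown. Data Collection is equally brief on the PEEP/FiO2 chart, which is optional under the same criteria and whose compliance is also assessed without restating the exemption. This stands in part: inclusion of all scores is the plain reading of an unrestricted percentage, not an explicit statement. It does not dispose of the point, because the sedation rule appears twice without a condition, once in the very sentence that gives the weaning term its condition.

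The second reply is about size, and most of it stands. Only extreme scores count, so permitted sedation to SAS 2 is not penalised. Four of the six suspension criteria are not about sedation. The criteria for a pressure support trial also keep out patients with a sedated procedure planned within 48 hours, which limits criterion (i) early on. At vn = 18% with 10% of scores exempt, a false fail needs ve = (0.25 − 0.90 × 0.18) / 0.10 = 88%.

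A reader might also infer three stronger things that the document does not support:

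- **That the bar is equally at risk in both directions.** A false pass needs exempt scores to be better controlled than governed ones. That runs against the expectation of deeper sedation in exempt periods, and the document offers no mechanism for it.
- **That half of the primary outcome is affected.** Sedation is one of two named components, but no weights are given, and SBT compliance has its own 75% bar.
- **That the comparison between arms is biased.** The central hypoventilation alarm is a criterion only in Automated Weaning, so exempt time could differ by arm. No frequency is given, and the acceptability bar is not a between-arm test.

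**Conclusion.** The point holds as an inconsistency in the definition. The document waives sedation titration in defined periods and carries that waiver into the weaning component of the primary outcome, but not into the sedation component judged against the same bar.

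The main risk is a falsely failed bar. Its size cannot be fixed from the document. In the assumed scenarios for a false fail, the exempt share needed runs from about 8% to about 38%, and at about 5% the verdict is safe unless the mandatory-period rate is already near 25%. Dilution toward a false pass is arithmetically possible but less plausible. This should be fixed, but it does not invalidate the design: no element of randomization or treatment is shown to be wrong.

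**What to change.** In Data Collection and Statistical Analyses, restrict both numerator and denominator of sedation compliance to SAS or RASS scores recorded while no suspension criterion from section d) is met, in line with the weaning rule. Report the exempt scores separately by arm, with their number and out-of-range percentage, and give the all-scores percentage as a sensitivity figure.

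The text change is about one sentence in each place. Criterion status is already needed to classify off-protocol hours. The added work is to match each sedation score to that status, including any time when a criterion was met but the patient stayed on the assigned weaning strategy. The denominator will be somewhat smaller. The change is to the analysis only and leaves the clinical sedation rules as they are.
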